### Interventions

Regardless of group allocation, both groups will receive physical therapy at the hospital once or twice at least for 3 months. Hospital-based physical therapy will be performed for 1 h in combination with joint mobilization and modality (heat and electrical stimulation by physical therapists with more than 10 years of treatment experience). The therapist will be blinded to the assigned intervention group of the participant.

All patients will be instructed to exercise at home at least once a day with precautions for each exercise stage, exercise posture, method, and frequency. Depending on group allocation, there will only be a difference in the way home exercise is performed, with no difference in the program itself or the type/duration of the exercise. All patients will receive an assistant bar, a yellow elastic band and 0.5-kg dumbbells required to perform the exercises. Exercise will consist of 3 stages according to the adhesive capsulitis stage (i.e., stage I is freezing, stage II is frozen, or stage III is thawing). Every month during the intervention period, the exercise stage will change according to the stage of the adhesive capsulitis. All exercises will consist of a warm-up, scapular stabilization, shoulder ROM exercises, and shoulder stretching. The details of the exercise differ by step (Additional file 2), and strength training is added from the frozen stage (stage 2). The stepwise exercise will be the same for both groups and consist of 11–16 types of exercise, ten times per set, with a total exercise time of 30–40 min. Exercise contents of each stage were determined based on the literature [14, 15].

### Telerehabilitation

For the telerehabilitation, an UINCARE Home+ (UINCARE corp., Seoul, Korea) will be utilized. The UINCARE Home+ will be rented for 3 months and installed at the patient’s home. The main function of this hardware is to capture users’ 25 joint movements in real time through infra-red and motion sensors of 3-dimension depth camera (Xbox One Kinect for Windows®, Microsoft, USA). Exercise will be carried out by the patient viewing and following guide videos. Users can see their movement in the center of the screen as well as the exercise number, holding time, and a small exercise video on the side of the screen. If the user completes the exercise session, they can obtain real-time feedback on performance and accuracy on the result screen (Fig. 3).

**Fig. 3 Fig3:**
[figure not shown]
UINCARE Home+ (left) and screen during exercise with real-time feedback (right) (A: guide video, B: holding time, exercise set and number)

The telerehabilitation protocol using the UINCARE Home+ is shown in Fig. 4. First, the physician will diagnose the patient’s stage of adhesive capsulitis and prescribe a corresponding exercise program. The UINCARE company device manager creates the user account and then, independent researchers set up the prescribed exercise program on the administrator page. The UINCARE Home+ will be delivered by the company, installed at the patient’s home, and the patient will be trained on how to use it. During the intervention period, independent researchers will monitor performance, accuracy, and check individual exercise schedules through the administrator page. Every month, the researcher will enquire of the related problem and encourage the patient to exercise at least once a day.

**Fig. 4 Fig4:**
[figure not shown]
Protocol for interactive augmented reality-based telerehabilitation

### Brochure (usual care)

This group will be offered a brochure in accordance with the patient’s diagnosed adhesive capsulitis stage. They will be asked to record the number of exercises in their exercise log book. During the intervention period, participants were asked to submit the exercise log book every month.

### Outcomes

Outcome measures that will be assessed by a blinded physical or occupational therapist and time points are described in Table 1.

**Table 1 Tab1:**
[figure not shown]
Summary of baseline screening, assessment, and follow-up during study visits

*SPADI* Shoulder pain and disability index, *SF-36* 36-Item Short Form Survey, *EQ-5D-5L* European Quality of Life Five Dimensions Five Level Scale, *COPM* Canadian Occupational Performance Measure

*Digital healthcare system rehabilitation group only

### Primary outcomes

The primary objective of this protocol is to determine the additive effect of interactive AR-based telerehabilitation in conjunction with hospital-based physical therapy on passive range of motion (PROM) for patients with adhesive capsulitis 3 months post diagnosis. Therefore, the primary outcome will be the change in PROM of the affected shoulder joint from baseline to 12 weeks after baseline assessment.

### Secondary outcomes

The secondary objectives of this protocol are to determine the additive effect of interactive AR-based telerehabilitation in conjunction with hospital-based physical therapy on 1) pain intensity; 2) activities of daily living; 3) quality of life; and 4) shoulder disability over time. Therefore, the secondary outcomes will be active ROM, pain measured with the numeric rating scale, shoulder pain and disability index, 36-Item Short Form Survey, European Quality of Life Five Dimensions Five Level Scale, and Canadian Occupational Performance Measure. Along with the RCT, a satisfaction questionnaire (Additional file 3) and safety assessment will be conducted for both the system and equipment.

As secondary outcomes, active range of motion (AROM), pain and disability of the affected shoulder joint, quality of life, and activities of daily living (ADL) will be considered at all follow-up assessments. The satisfaction questionnaire for interactive AR-based rehabilitation will be evaluated only in the intervention group after 12 weeks.

Supine measurements of PROM and AROM of the affected shoulder will be obtained with the participants lying in a supine position. Shoulder forward flexion, abduction, and external and internal rotation with a 90° shoulder abduction will be measured with an electronic goniometer in units of 1°. All ROMs of each participant will be assessed as described by Kelly et al. [14].

The pain intensity at resting and activity will be evaluated by a 11-point Numeric Rating Scale (NRS) [16] for the past week, with 0 and 10 representing “no pain” and “the worst possible pain”, respectively Participants will be asked for an average perceived pain intensity in ADL.

Shoulder pain and disability for the past week will be assessed using the Shoulder Pain and Disability Index (SPADI), consisting of two subscales with a total of 13 items (five items for pain and eight for disability) [17]. Patients will report a level of difficulty performing ADL due to pain and limit of motion. The final score will range from 0 to 130 with a percentage score of 0 indicating less shoulder disability and 100 indicating more shoulder dysfunction.

Quality of life will be assessed using the 36-Item Short Form Survey (SF-36) and the European Quality of Life Five Dimensions Five Level Scale (EQ-5D-5L). The SF-36 consists of eight scaled scores as a patient-reported survey of overall health. Scores for each domain range from 0 to 100, with a higher score defining a more favorable health status [18]. The EQ-5D-5L measures the health-related quality of life of patients. A validated model for the Korean population may be used to interpolate quality weights for all EQ-5D-5L health states [19]. This scale is numbered from − 0.066 to 0.904. Utility will be applied to the economic evaluation of both the intervention and control groups.

The ADL assessment will be used by the Canadian Occupational Performance Measure, which compares the importance, performance, and satisfaction of activities that present problems in daily life and can identify the five most problematic activities before and after intervention. Performance and satisfaction can be obtained by summing the scores of all items and then dividing it by the number of items. If the re-evaluation value minus the pre-evaluation value is 2 or more, intervention is significant [20].

### Sample size calculation

The target sample size was calculated through consultation with an in-hospital statistics team. The primary hypothesis was that there would be a significant difference in the amount of change in PROM before and after 3 months for the digital health care and control groups. The ROM consists of flexion, abduction, external rotation, and internal rotation of the shoulder joint. When the standard deviation of the variation is 18.64, 16.79, 11.22, and 11.65, respectively, and the difference between the two groups variation is expected to be 15, 15, 10, 10, or more, respectively, based on the results of the existing studies [21–25], 35 people per group are required for a significance level of 5% (a significant level of 0.05/4*100% of each hypothesis) and 80% statistical power. Assuming an expected dropout rate of 25%, we require at least 47 participants per group.

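### The four primary PROM directions are each given a fixed 0.05/4 level; Holm's step-down rule would hold the same 5% family-wise error and sometimes reject more, at almost no cost

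*Protocol article*

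**What the plan says.** All of this is in the protocol article.

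- **Sample size calculation, hypothesis.** "The primary hypothesis was that there would be a significant difference in the amount of change in PROM" over three months. The components follow: "The ROM consists of flexion, abduction, external rotation, and internal rotation of the shoulder joint".
- **Sample size calculation, level.** The overall level is 5%, and each direction is given "a significant level of 0.05/4*100% of each hypothesis". The target for power is 80%, and the result is 35 per group. This is the only multiplicity rule in the document. It does not mention a step-down, an ordering or any recycling of alpha.
- **Sample size calculation, assumptions.** A standard deviation of the change is given for each direction (listed under the inputs below). On the effect sizes, the text says that "the difference between the two groups variation is expected to be 15, 15, 10, 10, or more, respectively". An effect is therefore planned in every direction.
- **Statistical analysis.** The primary comparison is an independent t-test if the data are normal. The level is 5% with a 95% confidence interval. The four-way split is not repeated.
- **Participants.** 100 patients are to be enrolled, allocated 1:1.

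**The concern.** Once there are four primary hypotheses and an overall 5%, some multiplicity rule is needed. The one written down, 0.0125 for each, protects the 5%, but Holm gives the same protection and is never less powerful. Holm also needs no assumption about how the directions correlate.

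The gain comes when several hypotheses are false, because each rejection relaxes the threshold for the next. That is the situation this protocol plans for: one joint, one treatment, and a difference expected in all four directions.

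An illustration with invented p-values of 0.001, 0.004, 0.010 and 0.030:

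- Bonferroni rejects three and calls the fourth negative, because 0.030 > 0.0125.
- Holm compares them in order with 0.0125, 0.0167, 0.025 and 0.05, and rejects all four.

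What is at stake is a patchier primary result than the 5% error budget requires. The trial's validity is not at stake.

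**Working it through.** **1. Inputs.** All are from Sample size calculation unless marked.

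| Direction | Difference (°) | SD of change (°) |
|---|---|---|
| Flexion | 15 | 18.64 |
| Abduction | 15 | 16.79 |
| External rotation | 10 | 11.22 |
| Internal rotation | 10 | 11.65 |

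Alpha is 0.05/4 = 0.0125 per direction, power 80%, dropout 25%. Two assumptions are needed:

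- *Sidedness* is not stated. Two-sided is assumed because it gives 35 (one-sided 0.0125 gives 30).
- *Correlation* between directions is not given. A common value is assumed, with a range shown.

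**2. Reproducing the plan's figure.** n per group = 2·SD²·(z₁₋₀.₀₀₆₂₅ + z₀.₈₀)² / Δ², where (2.498 + 0.842)² ≈ 11.15.

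- Flexion: 2 × 18.64² × 11.15 / 15² = 34.4, so 35
- Abduction: 27.9, so 28
- External rotation: 28.1, so 29
- Internal rotation: 30.3, so 31

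The maximum is 35, and 35/0.75 = 46.7, so 47. Both stated figures reproduce. An unadjusted two-sided 5% would give 25, so the split was used for sizing. The exact t-test needs 37 for flexion (36.03 rounded up), a difference of two patients.

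**3. Bonferroni power by the exact t-test** (flexion, abduction, external rotation, internal rotation).

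- 35 per group: 78.6%, 87.6%, 87.4%, 84.4%
- 37 per group: 81.3%, 89.6%, 89.5%, 86.7%

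The second row matters because 100 enrolled is 50 per group, and 50 × 0.75 = 37.5.

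**4. Why Holm keeps the 5%.** Suppose m of the four null hypotheses are true. When Holm first reaches a true null, at least m hypotheses are still untested, so the threshold there is at most 0.05/m. The chance that any of m true nulls has a p-value that small is at most m × 0.05/m = 0.05, whatever the correlation. Every Holm threshold is at least 0.0125, so nothing Bonferroni rejects is lost.

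**5. Bonferroni against Holm by simulation.** 60,000 trials per row, four-variate normal, two-sample t-tests, 35 per group, planned effects true in all four directions. Entries are Bonferroni → Holm, in %.

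| Assumed correlation | Flexion | Abduction | External rot. | Internal rot. | All four | At least one |
|---|---|---|---|---|---|---|
| 0 | 78.5 → 89.9 | 87.4 → 94.5 | 87.5 → 94.7 | 84.4 → 93.1 | 50.5 → 78.0 | 99.96 both |
| 0.3 | 78.3 → 88.9 | 87.5 → 93.6 | 87.4 → 93.6 | 84.5 → 91.9 | 57.4 → 80.1 | 99.2 both |
| 0.5 | 78.3 → 88.1 | 87.4 → 92.8 | 87.4 → 92.8 | 84.5 → 91.4 | 62.3 → 81.8 | 98.3 both |
| 0.8 | 78.7 → 87.6 | 87.6 → 91.4 | 87.5 → 91.4 | 84.6 → 90.0 | 71.0 → 85.7 | 94.6 both |

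- At correlation 0.7 the all-four figure goes from about 68% to 84%.
- At 37 per group flexion goes from about 81% to 90-91%.
- In no simulated trial did Bonferroni reject a direction that Holm did not.

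**6. Limits of the gain.**

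- *Only flexion truly different:* flexion power is about 78.5% under Bonferroni and 78.6% under Holm. False rejection among the other three is 2.6-3.7% under Bonferroni and 3.1-4.7% under Holm, both within 5%.
- *No true effect:* family-wise error is the same for both rules, 3.2-4.9% across the correlations.
- *True effects at 70% of plan, correlation 0.5:* flexion goes from 42% to 53%, and all four from 18% to 37%.

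**The case against.** **The split appears only where the trial is sized.** Sizing at 0.05/4 is also a conservative way to size a Holm analysis, and the analysis section names no procedure. This stands in part. The sizing text is compatible with Holm, and a fuller analysis plan may name a rule. But 0.05/4 for each hypothesis is the only rule the document gives, so a reader would apply it as written.

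**A reader might infer from the analysis section that each direction is tested at an unadjusted 5%.** Holm would then be the stricter rule: at 35 per group flexion power is 91% unadjusted, against 88% under Holm at correlation 0.5. The documents do not settle this reading. The analysis section does not say that 5% applies per direction, and doing so would break the overall 5% in the sizing section: with four independent true nulls the error would be 1 − 0.95⁴ = 18.5%. What stands is that the rule has to be written into the analysis section.

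**A reader might infer that Bonferroni is wrong here, or that the trial is underpowered.** Neither is supported. Bonferroni protects the 5%, matches the sample size and gives simple simultaneous intervals. At about 37 evaluable per group every direction exceeds 80%.

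**The largest gain is for all four directions, which the plan does not set as its success criterion.** This stands. If all four were required, no split of alpha would be needed. The all-four figure only describes how complete the result would look.

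**Conclusion.** The point holds as a cheap improvement. The fixed 0.0125 per direction is valid, and the sample size is right for it. Holm has the same error guarantee and is at least as powerful for every direction.

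The per-direction gain of about 4 to 11 points is largest for flexion, the direction that fixes the sample size. It rests on the planned differences and SDs holding in all four directions, on two-sided tests, and on a common correlation of 0.3 to 0.7 that is assumed because the document gives none. That Holm dominates Bonferroni and holds the 5% rests on none of these. The gain shrinks as fewer directions truly differ, and Holm does not make a first significant result any likelier.

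**What to change.** In Statistical analysis, before the data are analysed, state that the four PROM p-values are tested by Holm's procedure at an overall two-sided 5%. They are ordered from smallest to largest and compared with 0.05/4, 0.05/3, 0.05/2 and 0.05, stopping at the first failure, and benefit is claimed only for the directions rejected. Say that this replaces both the fixed 0.0125 and any unadjusted 5% per direction.

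Keep 35 and 47 per group as the conservative size. For the four primary directions, report 98.75% simultaneous intervals (100% − 5%/4) instead of the general 95% ones.

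The cost is one or two sentences, with no extra patients, visits or alpha. Data management rules out an interim analysis, so nothing complicates the step-down. The one drawback should be stated in the plan: a 98.75% interval can include zero for a direction that Holm rejects.

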### Data management

All participant data will be collected and coded by research team members and will be stored in the secured platform accessible only research team members. Backup database will be updated regularly. The anonymized dataset will be available on request to the corresponding authors. No interim analysis will be performed prior to the end of the study.

### Statistical analysis

Subject demographics will be calculated using descriptive statistics. Kolmogorov–Smirnov test will be performed to assess the distribution of data. To compare baselines between the two groups, an independent t-test and chi-square test will be conducted. To compare the mean difference, if primary outcome (PROM) data in both groups is found to be normally distributed, we will perform an independent t-test, not Mann-Whitney test. How to handle missing data will be applied depending on distribution of data after study completed.

To investigate the effects of the interventions and differences between groups for secondary outcomes, a mixed effects model or generalized estimating equations will be conducted, with one between-subject factor (group: intervention and control) and one within-subject factor (evaluation time: baseline, 4-week, 8-week, 12-week, 18-weeks, and 24-week follow-ups). All data will be analyzed using IBM SPSS Statistics version 20.0 (Armonk, New York, USA) and a significance level of 5% will be set with a 95% confidence interval.

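### A normality check on the trial's own outcome data chooses the primary test, so the primary analysis may leave the mean difference in degrees on which the trial was sized

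*Protocol article*

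**What the plan says.** All references are to the protocol article.

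- **Primary outcomes:** "the primary outcome will be the change in PROM of the affected shoulder joint from baseline to 12 weeks after baseline assessment".
- **Sample size calculation:** this outcome is four variables: "The ROM consists of flexion, abduction, external rotation, and internal rotation of the shoulder joint". Each is a hypothesis tested at 0.05/4. The inputs are SDs of change ("When the standard deviation of the variation is 18.64, 16.79, 11.22, and 11.65, respectively") and differences in degrees ("the difference between the two groups variation is expected to be 15, 15, 10, 10, or more, respectively").
- **Statistical analysis:** "Kolmogorov–Smirnov test will be performed to assess the distribution of data". The aim of the primary comparison is introduced with "To compare the mean difference", and the rule is: "if primary outcome (PROM) data in both groups is found to be normally distributed, we will perform an independent t-test". The sentence ends by setting the Mann-Whitney test aside in that case.

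The article does not give the level of the normality check or its variant (with or without correction for an estimated mean and SD). It also does not say whether the choice is made once for PROM as a whole or separately for each direction.

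**The concern.** A t-test on change compares mean changes in degrees. That is the stated target and the quantity behind the sample size. Mann-Whitney compares ranks, in effect the probability that a patient in one group gains more than a patient in the other. It does not estimate the difference in means. Under the stated rule, the question answered by the primary analysis depends on a feature of the observed data that has nothing to do with the clinical question.

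If the rule is applied direction by direction, flexion might be reported as a mean difference and abduction as a rank contrast. Four hypotheses that share one alpha would then no longer be about the same kind of effect. Two analysts who use different variants of the check could also run different primary tests on the same data.

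**Working it through.** **1. The plan's own figure.** Inputs from the Sample size calculation section: SDs 18.64, 16.79, 11.22, 11.65; differences 15, 15, 10, 10; alpha 0.05/4 = 0.0125; power 80%. Two-sided testing is assumed because it reproduces the result.

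n per group = 2(z₀.₉₉₃₇₅ + z₀.₈₀)² × (SD/difference)² = 2(2.498 + 0.842)² × (SD/difference)² = 22.30 × (SD/difference)²

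| Direction | (SD/difference)² | n | Rounded up |
|---|---|---|---|
| Flexion | (18.64/15)² = 1.544 | 34.4 | 35 |
| Abduction | (16.79/15)² = 1.253 | 27.9 | 28 |
| External rotation | (11.22/10)² = 1.259 | 28.1 | 29 |
| Internal rotation | (11.65/10)² = 1.357 | 30.3 | 31 |

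The maximum is 35, and 35/0.75 = 46.7, so 47. Both stated figures reproduce, from a formula for a difference in means. With the noncentral t, flexion needs 36.03. A rank test on normal flexion data would need 36.03/(3/π) = 36.03/0.955 = 37.7, so about 38.

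**2. How often the rule would switch tests.** Assumptions: a 5% check (the level is not stated), run in each group and for each direction.

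- One direction, normal data, check of exact 5% size: 1 − 0.95² = 9.75%.
- At least one of four independent directions: 1 − 0.95⁸ = 33.7%. All four switch together with probability only 0.0975⁴ ≈ 0.01%, so nearly every switch gives a mixed set of tests.

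Simulation with 35 per group, four directions and 1,500 trials per setting; ranges cover correlations of 0 and 0.5 between directions:

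| Data | At least one switches, Lilliefors-type | Mixed set, Lilliefors-type | At least one switches, uncorrected (all mixed sets) |
|---|---|---|---|
| Normal | 31.9–33.7% | 31.9–33.7% | 0.2% |
| Skewness about 0.7 | 75.8–78.2% | 74.7–77.6% | 2.1–2.2% |
| Skewness 1.0 | 92.0–93.7% | 85.1–88.1% | 5.7–6.3% |

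Correlation between directions matters little. The variant of the check matters a great deal.

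**3. Type I error.** In the same simulations with no group difference, each direction was tested at 0.0125. Family-wise error was 0.037–0.057 for the two-stage rule (Lilliefors-type check) and 0.033–0.055 for the t-test always. The two are similar.

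**4. Power of the two tests.** 100 patients in two groups with 25% dropout leave 50 × 0.75 = 37.5, so 37 per arm. A pure shift of 15/18.64 = 0.80 SD was tested at two-sided 0.0125 in 6,000 runs:

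| Data | t-test | Mann-Whitney |
|---|---|---|
| Normal | 82% | 79% |
| Skewness −1 | 82% | 86% |
| t with 4 df | 82% | 91% |

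**The case against.** Five points can be made for the plan.

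- **The per-direction choice is not written.** The rule treats PROM data as one object. If the choice is made once, no mixture across directions can arise. This stands as a limit on the mixing argument. It does not remove the data-dependent choice, which would then move all four directions off the mean difference together.
- **The Mann-Whitney fallback is inferred from awkward wording.** Read literally, the sentence only rules Mann-Whitney out when the data look normal. That is true, but no other alternative is named, and on the literal reading non-normal data would have no primary test at all.
- **The 34% is an upper bound for normal data.** It needs a per-direction choice, a check of exact 5% size, and independent directions. The article names the Kolmogorov-Smirnov test without a correction. Uncorrected, the rule would almost always end in the t-test when data are normal. This stands, and the range has to be given.
- **Both branches and the trigger are written down.** It would be too strong to say that nothing is prespecified. What stays open is the variant of the check, its level and the unit of decision.
- **The rank test can be the better test.** With skewed or heavy-tailed changes it had 86% and 91% power against 82%. A reader might infer that the switch gains nothing at this sample size; for power that is not so. The simulation assumes a pure shift, however, and the article makes no such assumption that would let a rank result be read as a difference in degrees.

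**Conclusion.** The point holds in a limited form. The article states a rule by which the outcome data select the primary test, and one branch leaves both the stated target (the mean difference) and the basis of the sample size. Because the rule is stated, this is not a detail left to an unseen analysis plan.

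Its size depends on what is left open. If the choice is made per direction with a 5% check, the chance that at least one direction switches under normality runs from about 0.2% to about 34%. With skewness of 0.7 to 1.0 it runs from about 2% to about 6% uncorrected, and from about 76% to about 94% with a Lilliefors-type check. Quoting 34% as the expected rate would go beyond the documents.

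A reader might also infer that the two-stage rule inflates the false-positive rate, or that the sample size is wrong. Neither is supported: family-wise error was close to that of the t-test alone, and 35 and 47 both reproduce. The harm is to the fixed estimand and to the reading of the primary result. The case for change rests on keeping to the plan's own target, not on superior power of the t-test.

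**What to change.** Drop the normality check as a selector. State one mean-based comparison of the 12-week change in PROM for all four directions, whatever the distribution, each at the planned 0.0125. The planned t-test used unconditionally is enough; preferably, make the same comparison adjusted for the baseline PROM that is already collected. Robust or bootstrap standard errors are optional. Name Mann-Whitney as a sensitivity analysis for every direction.

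The cost is small. The stated 35 per group (47 with dropout) is unchanged, and no new data are needed. Recruitment began in March 2020, so the change should be documented before outcome data are compared between groups. If it counts as an important modification, it goes to the review board as the Ethics and dissemination section provides. The statistical price is some power relative to the rank test if changes prove skewed or heavy-tailed: about 82% against 86–91% at 37 per arm in the simulation above.

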## Methods/design

### Study design

This protocol will be a prospective multi-centered single-blinded two-armed RCT. The study design meets SPIRIT guidelines [13] and the SPIRIT Checklist are attached as Additional file 1. All eligible patients will be informed about this study and invited to participate by the outpatient doctor at the Physical Medicine and Rehabilitation clinic in Republic of Korea. All patients submit informed consent if they agree to participate in the study and principal investigator obtained the informed consent. After randomly divided into two groups with a 1:1 allocation, participants will be assessed in baseline. The intervention group will receive at least 3 months of hospital-based physical therapy in conjunction with home-based telerehabilitation. The control group will receive at least 3 months of hospital-based physical therapy in conjunction with a home-based exercise brochure provided by the hospital. The adhesive capsulitis stage will be evaluated at each follow-up by a physician, and exercises according to the stage will be prescribed. Outcomes will be assessed at the baseline and 1-month, 2-month, 3-month, 4.5-month, and 6-month follow-ups. Deviation of 7–15 days from each evaluation point will be allowed. Outcome measures will be performed by the same assessors, who will be blinded to the group allocation. The flow diagram of the study protocol is shown in Figs. 1 and 2.

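### The primary comparison of change in PROM makes no use of baseline PROM, although it is measured; adjusting for it is expected to be more precise and protects against chance imbalance

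*Protocol article*

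**What the plan says.** The Primary outcomes section states that "the primary outcome will be the change in PROM of the affected shoulder joint from baseline to 12 weeks after baseline assessment". The Sample size calculation section splits this into flexion, abduction, external rotation and internal rotation, each tested at "a significant level of 0.05/4*100% of each hypothesis".

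The Statistical analysis section chooses the test. If PROM is normally distributed in both groups, "we will perform an independent t-test, not Mann-Whitney test". Mann-Whitney is therefore implied otherwise. No covariate is named for either branch. A mixed model or GEE is planned for the secondary outcomes only, with group and time as its factors. Baseline differences are to be tested, but nothing is said about acting on them.

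The Study design section has outcomes assessed at baseline, so baseline PROM is available for every direction. The section on randomization describes blocks of four and mentions no stratification. A statistical analysis plan may exist and is not shown, but here the article itself fixes the unadjusted test.

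**The concern.** Change from baseline contains the baseline value. Unless the slope of 12-week PROM on baseline PROM is exactly 1, change is correlated with baseline. A comparison of raw change then leaves explainable variation in the error term. It also lets a chance difference between the groups in starting PROM carry over into the estimated effect.

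At stake are precision and robustness in a trial of modest size whose significance level is shared among four directions. Flexion, which sets the sample size, has little power to spare. Because baseline tests are planned with no rule for responding to them, the plan also leaves room for an adjustment decided after the data are seen. Naming the adjustment in advance closes that gap.

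**Working it through.** **Inputs from the article.** The SDs of change: "the standard deviation of the variation is 18.64, 16.79, 11.22, and 11.65, respectively". The differences: "the difference between the two groups variation is expected to be 15, 15, 10, 10, or more, respectively". The level is 0.05/4 = 0.0125 per direction, with "80% statistical power", 1:1 allocation and 25% dropout. Sidedness is not stated; two-sided is assumed, and it reproduces the stated figure.

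**Assumed inputs.** The article gives neither the correlation r between baseline and 12-week PROM nor the SD at either time. I take r from 0.3 to 0.9 and, at first, equal SDs. Centre and stage are given no prognostic value.

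**Step 1: the plan's own figure.** n per group = 2 × (SD/difference)² × (2.498 + 0.842)². For flexion this is 2 × (18.64/15)² × 11.15 = 34.4, so 35. The other directions need 28, 29 and 31. The maximum is 35, and 35/0.75 = 46.7, so 47. Both match the article. The t-based requirement for flexion is 37.

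**Step 2: unadjusted precision for flexion at 35 per group.** SE = 18.64 × √(2/35) = 4.46 degrees. Power from the noncentral t distribution is 78.6%.

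**Step 3: effect of adjustment.** With a common SD s, the variance of change is 2s²(1 − r) and the residual variance after adjustment is s²(1 − r²). Their ratio is (1 + r)/2. Fitting three covariates (baseline, centre, stage) in 70 patients inflates the variance by about 1 + 3/64 = 1.047. The SE ratio is therefore √[(1 + r)/2 × 1.047].

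| r (assumed) | SE ratio | SE, flexion | SE reduction | Power, flexion | n per group for 80% power |
|---|---|---|---|---|---|
| unadjusted | 1 | 4.46 | – | 78.6% | 35 |
| 0.3 | 0.825 | 3.68 | 17.5% | 93% | 23 |
| 0.5 | 0.886 | 3.95 | 11.4% | 89% | 26 |
| 0.7 | 0.943 | 4.20 | 5.7% | 84% | 30 |
| 0.8 | 0.971 | 4.33 | 2.9% | 81% | 31 |

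Power is t-based with 65 degrees of freedom when adjusted. The last column uses the normal approximation without the covariate charge. Simulation (6,000 runs per r) gave SE ratios of 0.82, 0.88, 0.94 and 0.99 at r = 0.3, 0.5, 0.7 and 0.9. With baseline as the only covariate the charge is smaller, 1 + 1/66 = 1.015, so the table is slightly conservative for that model.

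**Step 4: where the gain disappears.** Three covariates break even when they explain 1 − 1/1.047 = 4.5% of the variance of change. Under equal SDs, baseline explains (1 − r)/2, which is 5% at r = 0.9. With k the ratio of follow-up SD to baseline SD, the variance ratio is k²(1 − r²)/(1 + k² − 2rk). At r = 0.7 and k = 1.2 (assumed) this is 0.734/0.760 = 0.966, and 0.966 × 1.047 = 1.01, so there is no gain. With k below 1 the gain at that r would be larger.

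**Step 5: chance imbalance.** Under equal SDs the change-score estimate shifts by r − 1 degrees per degree of baseline difference. Simulation gave −0.70, −0.51, −0.31 and −0.10 at r = 0.3, 0.5, 0.7 and 0.9; the adjusted estimate moved by less than 0.02. At r = 0.5 the baseline SD is 18.64/√(2 × 0.5) = 18.64, so a one-SD chance imbalance is 18.64 × √(2/35) = 4.46 degrees. It moves the t-test estimate by 0.5 × 4.46 = 2.2 degrees. Averaged over randomisations, both methods recovered the true 15 degrees.

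**The case against.** The strongest reply is that nothing here is wrong. The outcome is change, the trial is sized on the SD of change, and the test compares mean change. The stated 35 and 47 are correct for that test. With 100 enrolled and 25% dropout, about 37 per group remain, which meets even the t-based requirement for flexion. The four-way split of alpha is already in the sample size. All of this stands, so the point is an improvement and not the correction of an error.

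Four stronger readings are tempting, and the documents support none of them.

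- A reader might infer that the t-test on change is biased. It is not, over repeated randomisation. Only the estimate given the imbalance that actually occurs is shifted.
- A reader might infer that selecting patients with at least 30 degrees of restriction distorts the comparison through regression to the mean. The criterion applies to both groups alike, so its expected effect cancels between them.
- A reader might infer that centre and stage must be in the model because the design is "This protocol will be a prospective multi-centered single-blinded two-armed RCT" and stage determines the exercise programme. The article does not show that either predicts change in PROM, and it describes no stratification by either. Baseline PROM carries the case.
- A reader might take the large-sample gain at face value, with flexion power rising from 81% to 95%, 92% or 88% at r = 0.3, 0.5 or 0.7. Those figures use a normal approximation and charge nothing for the covariates. They are too favourable for about 70 patients.

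It is also fair to say that recruitment has begun, so this would be an amendment. That is a modest administrative cost.

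**Conclusion.** The point holds as one of efficiency and robustness. The planned test is valid, but it sets aside a baseline measurement already in hand. An adjusted analysis is expected, though not guaranteed, to be more precise, and its estimate does not move with baseline imbalance.

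For r between 0.3 and 0.8 the SE reduction runs from 17.5% down to 2.9%, and adjusted flexion power from 93% down to 81%. These figures rest on the assumed r, equal SDs, a two-sided level and 35 evaluable per group. The documents fix neither r nor the SD ratio, so the size of the gain is uncertain. The conclusion applies equally if the normality check leads to Mann-Whitney, since that test is also unadjusted. The sample size needs no revision on this account.

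**What to change.** For each of the four PROM directions, name one primary analysis: a linear model (ANCOVA) of 12-week PROM on group, with baseline PROM of the same direction as covariate. Modelling change in place of the 12-week value, with the same covariate, gives the same group effect. Report the adjusted difference in degrees with its confidence interval at the multiplicity-adjusted level (98.75%, from 0.05/4), and keep the unadjusted t-test as a supportive analysis.

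Centre and baseline stage may be added if named in advance. They cost two degrees of freedom, and the documents do not show that they are prognostic.

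The cost is an amendment. No new data or patients are needed, and standard software fits the model. Make the change before unblinded data are seen and report it to the institutional review board, as the Ethics and dissemination section requires for important modifications.
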